## Economic evaluation

### Cost effectiveness

The primary objective of the economic evaluation is to identify the within study incremental cost effectiveness ratios; the costs and benefits of the use of silicone compared to the costs and benefits of alginate over the duration of the study. Use of incremental cost effectiveness ratios will enable comparison of the additional financial costs imposed use of silicone over alginate with any additional benefits it delivers.

The primary analyses will take the perspective of the service provider including the costs of health and social care. In line with the clinical study patient data will be collected over the course of the dental construction and assessment period. The within-study analysis will estimate the expected incremental cost per point decrease in OHIP-EDENT score. In addition a secondary analysis will use quality adjusted life years (QALYs) outcome measures. The estimation of QALYs requires the production of utility weights for each health state observed in the study population. We will use the EQ-5D (Euroqol) instrument for this purpose
[19,20]. The EQ-5D is a very simple instrument to complete and will be collected at the same time and using the same methods as the other outcome data. This will limit the need to interpolate quality of life between observation points and the associated inaccuracy in the estimation of the health related quality of life differences between the interventions.

Health resource use associated with each treatment modality will be collected during each dental visit to contribute to a health economics analysis of additional health financial costs related to treatment and the study. This will include the service provision together with use of community and hospital based health care attributed to the treatment. Community and hospital based health care will be collected by way of a short patient questionnaire completed in the clinic. The patient questionnaire will be designed to allow tick box completion wherever possible. Unit financial costs for health services resources will be obtained from national sources such as the PSSRU, the BNF and NHS reference cost database.

Whilst the primary analyses will adopt the perspective of the NHS and social services, secondary analysis will adopt a societal perspective taking account of productivity costs and out of pocket expenditures incurred by the patients. The patient questionnaire will also be used to collect this data (for example, travel expenses). The data for collecting the indirect financial costs associated with each intervention (for example, time away from work) will also be collected through the patient questionnaire. There is currently uncertainty about the best method for estimating productivity costs; we will adopt the recommended method.

### Analysis

The incremental cost effectiveness ratios will be calculated as the difference between the mean costs and difference in OHIP-EDENT score/QALYs in each arm. The non-parametric bootstrap method will be used to produce a within study probabilistic sensitivity analysis of the incremental cost effectiveness ratios. The expected incremental cost effectiveness ratio, a scatter plot on the cost effectiveness plane, the 95% cost effectiveness eclipse and the cost effectiveness acceptability curve will be presented. Given the duration of the study discounting is not required.

## Qualitative study

The objective of the qualitative component of the study is to provide, from the patient perspective an in-depth understanding of expectations around treatment, treatment preferences and user centred outcomes. These are intended to complement the use of standardised tools (Likert Scales and Oral Quality of Life Questionnaire). They will be conducted at two points in time: in the course of scheduled visits to the dentist when the new dentures are being constructed, and at final assessment of the new adjusted dentures, at the end of the study.

### Sampling strategy

From among those consenting to be interviewed, a purposive sample of 18 patients will be initially selected to reflect dimensions of interest in terms of experience of tooth loss and expectations of treatment: age (under 40 years; between 41 and 60 years; 61 + years); gender; length of time with a full set of dentures (under 10 years; 11–20 years; 21 years and over); and socio-economic circumstances (housing tenure and 4-digit postcode. The sample size is sufficiently small to facilitate the collection of ‘information rich’ data (in-depth, detailed and nuanced); whilst being large enough to include patients whose experiences may differ in patterned ways. Thus the findings will enable insight into the social contexts that shape perceptions, meanings and experiences, complementing and extending those drawn from use of structured data collection methods and statistical analysis. We will, however, review the sample size in light of the data obtained leaving open the possibility of recruiting up to five further participants if it appears that themes emerging from the completed interviews require further exploration.

### Data collection

Using a loose topic guide, the first set of interviews are aimed at developing understanding about the meaning and significance of tooth loss, its course over time, the strategies employed to manage it, accessing treatment, treatment choices, preferences and expectations about outcomes. We will explore how tooth loss and denture related problems have impacted over time on patients’ behaviour in both public and private domains as they go about their daily lives; and affected social relationships, leisure pursuits, social activities, diet and eating pattern. We will examine impact on self-esteem and sense of self and the coping strategies people have employed to manage the difficulties encountered. The interviews will also examine what patients would most value as an outcome of good fitting dentures; their expectations about the kinds of changes they anticipate and what changes they would most value. A key difficulty in any assessment of life quality is that it is bound up with individual expectations. Yet expectations may be altered as a result of changing circumstances – whether lowered or heightened – posing a problem of measurement of quality of life. Developing an in-depth picture of experiences, behaviour, coping strategies and expectations relating to edentulous status will offer a clearer understanding of how and in what ways the new dentures affect those dimensions of life quality that are important to patients with different characteristics.

These qualitative interviews then will be guided by a list of topics to be covered rather than a set of pre-determined questions. The intention is to provide patients with the opportunity to talk about things that are salient to them and at the pace dictated by them within the framework provided by the topic guide. It is anticipated that interviews will last around an hour. Their content and structure will be discussed with our patient and older people’s reference/advisory groups.

A second set of interviews will be carried out with these patients at the end of the final assessment of their new adjusted dentures. We will examine patients’ experience of the intervention, what factors drove their choice of denture, any difficulties they might have had in stating a preference. We will also examine the relationship between prior expectations and actual experience with the new dentures including changes that may have occurred in behaviour, social relationships, social activities, diet and eating patterns; and if and in what ways the new dentures have made a difference to those dimensions of life quality on which they place high value. We anticipate that these interviews will also last around an hour. Topic guide for both interviews will be refined through involvement of our PPI representatives and older members of Caring Together that comprise our reference group, in a workshop organised prior to the commencement of the study.

### Data analysis

All of the interviews will be audio-taped, fully transcribed and analysed using a computer assisted qualitative analysis package. A grounded theory approach to analysis will be employed
[21], proceeding through the interplay between induction and deduction. Themes and patterns will be identified through open coding and categories and their constituent properties will be developed through comparing and contrasting coded segments. Of particular interest is the extent to which such factors as age, gender, length of time without teeth and socio-economic status impact on user centred outcomes and quality criteria and preferences.

## Discussion

Prosthodontic research has historically had a lack of RCT evidence
[8]. RCTs published in the prosthodontics literature have been reported poorly, lacking details regarding the details of randomisation and blinding which calls into question the quality of the studies themselves
[22]. This indictment of academic prosthodontics was a challenge for future researchers.

Carlsson looked at the lack of RCT evidence and went on to suggest that it is “not probable that comparisons between dentures made with varying materials and methods would lead to significant differences”. However the opinion of the authors is different; we believe the reasons for the lack of success with denture RCTs is the quality of protocol design coupled with twin problems within prosthodontics of multiple confounding variables and a sensitive meaningful outcome measure. The authors have accepted the challenge implied by Jokstad to design and execute a productive prosthodontic RCT protocol to CONSORT reporting standards. This paper gives full details of the protocol and the study for which it was designed.

This patient-centred study has been designed to address a key question in the construction of complete dentures, whether impression material has an impact on subsequent comfort and function of the constructed denture and whether that denture can be adjusted to the satisfaction of the patients. A crossover design has been used to eliminate many of the potentially confounding variables found in denture construction; patients are given 2 sets of dentures and act as their own control. This requires attention to the detail of the duplication techniques for the dentures
[16] to ensure the dentures are similar in all aspects apart from the impression material used at the secondary impression stage. In doing this, any preferences expressed can be reliably attributed to the impression material and not any other aspect of the denture construction. Additionally, a habituation period has been included in this study to guard against the potential for bias seen in other crossover studies
[9] that patients may prefer the denture they try in the second study period, a bias that has been attributed to the fact that the new dentures can feel very different to the patients existing dentures and the first study period is spent habituating to the new feel of the dentures
[9,17]. This study has been blinded to patients, dentists and dental nurses by marking the dentures only with coloured acrylic dots and by ensuring that all adjustment of dentures is managed by a dentist not involved in their construction/fitting. The primary outcome has been chosen to cover both patient-centred considerations (patient preference for denture impression material, previously shown to be a sensitive and effective tool
[23,24]) and health-economic considerations (cost-benefits associated with each of the denture impression materials).

The use of complete dentures has a significant impact on the lives of edentulous patients and the quality of secondary denture impressions has the potential to affect both comfort and function of the resultant dentures. There is a dichotomy of opinion between the UK and USA as to which impression material provides the best set of dentures and a paucity of evidence to support either view; this study aims to fill that evidence gap.

The protocol described for this study has potential to be adapted to explore other aspects of denture construction in the future. The use of crossover design, patient preference outcome, attention to detail in denture duplication and the strict blinding and randomisation procedures are designed to deliver robust results and guard against bias.

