### Denture construction

The Prosthodontic Research Team at LDI has developed and published a method of producing two or more sets of dentures which are clinically similar apart from the one deliberate alteration which is to be the subject of an RCT
[16]. This methodology will be used to produce two sets of dentures which are clinically similar apart from the impression material that was used to provide the mould for the fitting surface of each denture.

The intervention at the clinical secondary impression stage is the subject of this study; the secondary impressions will be made with either alginate or silicone. To take the secondary impressions, two sets of similar, spaced (2 mm), unperforated, light-cured acrylic secondary impression trays will be constructed. A set of impression trays consist of an upper and a lower tray; each set will be numbered in the laboratory A or B. Clinically, the secondary impression trays will be trimmed to size in the mouth to remove any over extension. After trimming, the trays will be randomly allocated to either the alginate or silicone impressions. The impression trays allocated to the alginate side of the study will be ‘border moulded’ with greenstick compound in the standard way
[17] and alginate (Xantalgin®) impressions taken. The trays allocated to silicone will be ‘border moulded’ with silicone (express 3 M) and impressions taken with silicone (express 3 M). The order in which the impressions are taken will be randomised; the patients will be rested for comfort for approximately 30 minutes between taking the first set of impressions and taking the second set of impressions. If a clinically adequate impression is not achieved at the first attempt with either material the impression will be repeated, until clinical adequacy is achieved. The total time taken to make the impression and number of attempts will be recorded.

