Both sets of impressions will be immediately rinsed and disinfected using a proprietary disinfectant. After disinfection the alginate impressions will be wrapped in damp gauze and sealed in an airtight plastic bag; this is to comply with normal practice and the alginate manufacturer’s instructions. The silicone will be shaken dry and then placed in a plastic bag. The following day, both sets of impressions will be checked and cast with vacuum mixed dental stone. Once cast, the models produced will be thoroughly cleaned to remove all traces of alginate or silicone impression material. The models from the different impression materials will be permanently numbered by the Head of the Prosthodontic Research Laboratory (or an individual authorised to do so by the Chief Investigator) according to a randomisation schedule provided by the trial statistician. All dentists will be blind to which set of models came from which impression material.

In order to ensure similar dentures are constructed for both impression materials, the protocol for occlusal registration and wax trial insertion in the paper by Dillon et al
[16] will be followed. This protocol utilises silicone moulds of the occlusal and polished surfaces to shape and position teeth and surfaces of the duplicate denture. The dentures will be constructed with balanced occlusion and where possible given a balanced articulation on an average value articulator. Once construction of both sets of dentures is complete, the sets will be marked with a red or blue acrylic dot according to the sealed envelope containing the random allocation provided by the trial statistician, to randomise the order of wearing during the habituation period. Insertion and delivery of the completed dentures will proceed in the usual way.

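### The Discussion attributes any preference to the impression material alone, but border-moulding material also differs between the two sets in every patient, so the trial compares two impression techniques

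*Protocol article*

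**What the plan says.** The Discussion explains that patients act as their own control and that care in duplicating the dentures is needed "to ensure the dentures are similar in all aspects apart from the impression material used at the secondary impression stage". From this it concludes that "any preferences expressed can be reliably attributed to the impression material and not any other aspect of the denture construction". The Abstract and the Design section state the same premise in similar terms, and the Denture construction section says the method will produce "two sets of dentures which are clinically similar apart from the impression material that was used to provide the mould for the fitting surface".

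The Denture construction section then describes the secondary impression stage. Trays allocated to alginate are border moulded "with greenstick compound in the standard way" before the alginate impression is taken. Trays allocated to silicone are border moulded "with silicone (express 3 M) and impressions taken with silicone (express 3 M"), so one product serves for both steps.

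The same section gives different storage until casting the next day. For alginate, "After disinfection the alginate impressions will be wrapped in damp gauze and sealed in an airtight plastic bag", and the reason follows: "this is to comply with normal practice and the alginate manufacturer’s instructions". For the other set, "The silicone will be shaken dry and then placed in a plastic bag".

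**The concern.** The attribution sentence makes a causal claim with an exclusion: the material is responsible and no other part of construction is. That needs two sets differing in one factor only. By the protocol's own account they differ in at least two, because border moulding is a named step with its own substance on each side and, for alginate, its own cited source.

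At stake is what the trial may conclude. Both primary objectives, on preference and on cost-effectiveness, are framed by impression material. If the results are reported as an effect of silicone against alginate as such, the report claims something the design did not isolate. A difference in either outcome could come from the main material, the border-moulding material or both.

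**Working it through.** The point rests on no figure in the protocol, so the check sets the construction steps side by side and asks what the contrast between sets can identify.

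**Step 1. What is held equal and what is not** (Randomisation and blinding; Denture construction).

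| Step | Alginate set | Silicone set | Tied to material? |
|---|---|---|---|
| Tray design | spaced 2 mm, unperforated | same | No; trays allocated at random |
| Order of impressions | first or second | first or second | No; randomised |
| Border moulding | greenstick compound | silicone | **Yes, in every patient** |
| Main impression | alginate | silicone | This is the named intervention |
| Repeats | until clinically adequate | same rule | No |
| Disinfection | proprietary disinfectant | same | No |
| Storage to next day | damp gauze, airtight bag | shaken dry, bagged | Yes, but part of handling each material |
| Casting | next day, vacuum-mixed stone | same | No |
| Occlusal and polished surfaces | duplicated with moulds | same | No |
| Order of wearing | randomised | randomised | No |

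**Step 2. Which combinations exist.** Two impression materials and two border-moulding materials give 2 × 2 = 4 combinations. The protocol makes 2: alginate with greenstick, and silicone with silicone. Alginate with silicone borders and silicone with greenstick borders are made for no patient.

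**Step 3. What the contrast identifies.** Let U(m, b) be how well a patient would rate a denture made with main material m (A alginate, S silicone) and border material b (g greenstick, s silicone). Preference depends on the sign of

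U(S, s) − U(A, g) = [U(S, s) − U(A, s)] + [U(A, s) − U(A, g)].

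The first bracket is the effect of material with border moulding held fixed. The second is the effect of border moulding. U(A, s) is never observed, so the trial supplies one contrast for two unknowns. Splitting instead through U(S, g) fails likewise.

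**Step 4. Whether a design feature helps.** The crossover removes differences between patients; this is a difference within each patient, bundled with the treatment. The randomisations govern tray, impression order, wearing order and colour code, not border moulding. The duplication method shapes tooth position and polished surfaces, not the impression stage. The planned McNemar, ANOVA and Wilcoxon analyses all compare set with set.

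**Step 5. Range.** The sample size section plans for preference rates of 60% and 30%, a difference of 30 percentage points. If exactly that were observed, it would be compatible with material alone, with border moulding alone, with any mixture, or with effects in opposite directions. The documents give nothing to narrow this.

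**Step 6. Whether the sample size is touched.** With a two-sided 5% level (sidedness is not stated), 80% power, p the total proportion expressing a preference and d = 0.30, N = [1.96√p + 0.842√(p − d²)]² / d².

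- 10% no preference: p = 0.90, N = 76.1 (protocol 76).
- 20% no preference: p = 0.80, N = 67.4 (protocol 67).
- Dropout: 76 / 0.90 = 84.4, rounded up to 85 (protocol 85).

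The inputs are preference rates between two sets. Naming the sets more fully changes none of them.

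**The case against.** The best defence is that the sentence has a context. It follows the remark on duplication, so the other aspects it excludes may mean only what duplication controls, such as tooth position, occlusion and polished surfaces. The Denture construction section also locates the intervention at the secondary impression stage, and border moulding falls within that stage. Using each material with its accompanying technique is a legitimate pragmatic choice, and the article discloses the difference openly.

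Most of this stands, and it supports a comparison of techniques. It does not support attribution to the material to the exclusion of everything else in construction. If border moulding belongs to the intervention, the intervention is more than the impression material.

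Three stronger readings may tempt a reader:

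- *Storage is a second confounder.* The protocol justifies the alginate storage by normal practice and the manufacturer's instructions. Handling a material as it requires is part of using it.
- *Cost collection is deficient.* The protocol records total impression time and number of attempts, and resource use at each dental visit. A cost-effectiveness comparison should in any case cost each technique as delivered. Itemised consumables are detail that an article may leave to fuller documents.
- *Dentists will change the material, keep their border-moulding method and so misapply the result.* The article says nothing about how dentists border mould, so this is conjecture.

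**Conclusion.** The attribution sentence is wrong as worded. Border-moulding material coincides with impression material in every patient, so the trial can attribute a preference or a cost-effectiveness difference to one of two impression techniques but not to the material alone.

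A reader might infer that the preference comparison is therefore biased or invalid. It is not: it remains a randomised, blinded comparison of two defined techniques, and its sample size, significance level and power are unaffected.

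The size and direction of any border-moulding effect are unknown, and this trial cannot estimate them. It may be nil. The conclusion assumes only that border moulding, done on the tray just before the impression is taken, can contribute to the surface from which the denture is made. The protocol does not say how much.

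**What to change.** 1. In the Discussion, remove the exclusive attribution and say instead that a preference can be attributed to the impression technique.
2. In the Abstract, Design, Denture construction and Discussion, qualify the premise that the sets differ only in impression material by naming border moulding as part of the difference.
3. Define the compared interventions once, in Denture construction: alginate with greenstick border moulding against silicone with silicone border moulding, each handled as its material requires. The objectives and the economic evaluation can then keep their short labels and refer to that definition.
4. Word the eventual conclusions on preference and on cost-effectiveness in the same terms. Trial status says recruitment has ended and results are still to be reported, so this can still be done.

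No change to the clinical procedure, sample size, analysis or cost collection is needed. The cost is a few sentences and a slightly narrower claim.
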